## Abstract

**Background:**

Vitamin E from palm oil, known as the tocotrienol-rich fraction (TRF), has been shown to have immune-enhancing activity. To date, only one dose of TRF (400 mg daily) has been tested in a clinical trial. The proposed study will evaluate the immune-enhancing activity effects of lower doses (200, 100 and 50 mg) in a clinical trial using an influenza vaccine as the immunological challenge.

**Methods:**

A single-centre, randomised, parallel, double-blinded, placebo-controlled clinical trial with balance allocation involving five arms will be conducted. The healthy volunteers recruited will be randomly assigned to one of the arms, and they will be asked to take the respective supplements (400 mg, 200 mg, 100 mg, 50 mg of TRF or placebo) daily with their dinner. The volunteers will receive the influenza vaccine after four weeks. They will be asked to return to the study site four weeks later. A blood sample will be taken for the study at baseline, four and eight weeks. Primary outcome measures will be antibody levels to influenza, blood leucocyte profile and cytokine production. Secondary outcomes will be correlating plasma vitamin E levels with immune responses, plasma proteins and gene expression patterns. The findings from this study will be published in relevant peer-reviewed journals and presented at relevant national and international scientific meetings.

**Conclusions:**

The recent world events have created the awareness of having a healthy and functional immune system. Nutrition plays an important role in helping the immune system to function optimally. This study will show the effects of lower doses of TRF in boosting the immune response of healthy individuals and also elucidate the mechanisms through which TRF exerts its immune-enhancing effects.

**Clinical trial registration:**

Australian New Zealand Clinical Trials Registry (ANZCTR) [
ACTRN12622000844741] dated 15 June 2022.

**Protocol version:**

2

## Introduction

The host immune system plays a pivotal role in protecting the body from infectious agents and cancers.
^
1
^
^–^
^
4
^ Appropriate and effective immune responses are essential to distinguish foreign antigens, such as infectious agents (e.g. viruses, bacteria, parasites and fungi) and abnormal or malignant cells from normal “self” antigens to prevent unwanted immune responses. The immune system is characterised by two mechanisms, the innate and the adaptive immune systems. The innate immune system comprising monocytes, macrophages, neutrophils, natural killer cells, dendritic cells, and granulocytes serves as the first line of defence against foreign antigens, directly targeting and facilitating the activation of the adaptive immune system.
^
5
^
^–^
^
7
^ The T- and B-lymphocytes are the key players of the adaptive immune system. The lymphocytes are not the first line of defence against foreign antigens as these cells need to be appropriately activated upon antigen recognition. Once activated, the lymphocytes elicit a more efficient and specific immune response as well as develop immunological memory.
^
6
^
^,^
^
8
^
^,^
^
9
^

A well-balanced nutritional status is essential for maintaining normal immune function. Deficiencies in nutrients often lead to impaired immune system function; on the contrary, intake at suggested levels can lead to normal or enhanced immune function.
^
2
^
^,^
^
3
^
^,^
^
10
^ Nutritional interventions have powerful effects on activating the host immune system.
^
10
^
^–^
^
12
^ One compound is vitamin E, which consists of tocopherols and tocotrienols. The vitamin E from palm oil, known as the tocotrienol-rich fraction (TRF), is a mixture of tocotrienols (70%) and tocopherols (30%).
^
13
^
^,^
^
14
^ Several clinical and experimental model-based studies have shown that tocotrienols have several biological activities such as antioxidant,
^
15
^
^,^
^
16
^ lipid-lowering,
^
17
^
^,^
^
18
^ immune-enhancing,
^
19
^
^–^
^
21
^ anticancer,
^
22
^
^–^
^
24
^ neuroprotective,
^
25
^
^–^
^
27
^ and anti-diabetic.
^
28
^
^,^
^
29
^ Tocotrienols may cause these effects by acting at the epigenome, genome or protein levels.
^
30
^ Recently, it was reported that consuming TRF can also cause changes to the gut microbiome.
^
31
^
^,^
^
32
^

In an earlier study, we reported that daily supplementation of 200 mg TRF or α-tocopherol (α Toc) did not induce significant immunomodulatory changes in healthy human volunteers in the absence of any immunological challenge.
^
33
^ In a subsequent study, we included an immunological challenge in the form of tetanus toxoid (TT) vaccination in healthy individuals supplemented daily with 400 mg TRF. Daily supplementation of 400 mg TRF produced a significantly higher immune response to the TT vaccine.
^
19
^ A recent report showed that daily supplementation of 150 mg TRF for six months modulated some genes related to the immune system in healthy older adults.
^
34
^ In the literature, most studies have used a single dose of TRF to report their findings. To date, no studies have evaluated the dose-response effects of TRF supplementation on the host immune system. So, there is a need to evaluate the effectiveness of supplementing daily with lower doses of TRF (200, 100, or 50 mg) to boost immune response following an immunological challenge such as a vaccine. The influenza vaccine was chosen in this study as the vaccine model, as flu is a major problem faced by individuals worldwide.

## Objectives

This study aims to investigate the effects of different concentrations of TRF (400, 200, 100 or 50 mg) on the immune response to an influenza vaccine in healthy individuals and to elucidate the mechanism of action. Using high and low dosages is important to understand what may happen following TRF supplementation. This information can be used to develop this in a range of functionality. The specific objectives are (i) to compare antibody responses to influenza antigen following daily supplementation with TRF (400, 200, 100 or 50 mg) with placebo; (ii) to compare leucocyte profiles and cytokine levels in response to influenza antigen following daily supplementation with TRF (400, 200, 100 or 50 mg) with placebo; (iii) to identify differentially expressed plasma proteins following daily supplementation with TRF (400, 200, 100 or 50 mg) with placebo in the presence or absence of vaccination; and (iv) to correlate plasma vitamin E levels with antibody levels in volunteers with and without daily supplementation with TRF.

### Research question

Will daily supplementation of lower doses of TRF (400, 200, 100 or 50 mg) enhance the immune response to an immunological challenge such as the influenza vaccine?

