### Study hypothesis

The research hypothesis of this study is that daily supplementation of lower doses of TRF will enhance the host’s immune response to an influenza vaccine.

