## Discussion

At the start of 2020, a global public health challenge was caused by a novel coronavirus known as the severe acute respiratory syndrome coronavirus 2 (SARS-CoV-2).
^
37
^ This virus was named the novel coronavirus 2019 or COVID-19. COVID-19 was declared a pandemic by the World Health Organization (WHO) in March 2021. The pandemic has increased awareness of the need for a well-functioning immune system.
^
38
^
^,^
^
39
^ Nutritional interventions can potentially affect the host immune systems.
^
9
^
^–^
^
10
^ One such compound is vitamin E from palm oil. The vitamin E from palm oil is known as the tocotrienol-rich fraction (TRF), which contains tocotrienols (70%) and tocopherols (30%).
^
13
^
^,^
^
14
^ Several researchers have reported on the ability of TRF to modulate the host immune system. To the best of our knowledge, no studies investigated a dose-response curve using TRF supplementation and its impact on the host immune system. Previous studies have used high TRF concentrations, which may not be necessary to achieve the immune-enhancing effects in healthy individuals.

Furthermore, not many people may be able to afford a high dose of TRF. For any supplement, it is crucial to know what is happening biochemically at different dosages to understand the targeted effects as well as any side effects. It is important to use both high and low dosages in a study to fully understand what is happening in response to the intervention and develop this in a range of functionality. The influenza vaccine was chosen in this study as the vaccine model, as flu is a major problem faced by individuals worldwide.

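### The research question counts 400 mg among the lower doses, contradicting the Abstract and Introduction, and no named comparison relates a lower dose to 400 mg or describes the dose-response that motivates the trial

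*Protocol article*

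**What the plan says.** The protocol article uses the term lower doses in four places that carry the aim of the trial.

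- Abstract, Background: 400 mg is the dose already studied ("To date, only one dose of TRF (400 mg daily) has been tested in a clinical trial"), and the trial will "evaluate the immune-enhancing activity effects of lower doses (200, 100 and 50 mg) in a clinical trial".
- Introduction: the need is to "evaluate the effectiveness of supplementing daily with lower doses of TRF (200, 100, or 50 mg) to boost immune response".
- Research question: "Will daily supplementation of lower doses of TRF (400, 200, 100 or 50 mg) enhance the immune response".
- Study hypothesis: "daily supplementation of lower doses of TRF will enhance the host’s immune response to an influenza vaccine", with no list of doses.

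On comparisons, objectives (i) to (iii) set the four TRF doses against placebo. Objective (iv) correlates plasma vitamin E with antibody levels. The Outcomes section speaks of comparing the groups without naming pairs. The Statistical analysis section names tests against baseline and/or placebo only.

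On motive, the Introduction says that the dose-response of TRF on the immune system has not been evaluated, and the Discussion repeats that no dose-response curve exists and adds: "Previous studies have used high TRF concentrations, which may not be necessary to achieve the immune-enhancing effects in healthy individuals".

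**The concern.** Two things are at stake.

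**The answer to the research question.** The dose against which the others are called lower cannot itself be one of them. The Research question is the formal statement of what the trial asks, and it is the only place near the Study hypothesis that attaches a dose list to the term. A result confined to 400 mg could then be reported, correctly by that wording, as support for lower doses, although the Abstract and Introduction promise something else.

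**The dose-response aim.** The motivation concerns how the response changes with dose and whether high doses are needed. The comparisons that the article names are each dose against placebo or baseline. Significance against placebo at one dose and not at another does not show that the two doses differ, and significance at both does not show that they are alike. Neither the contrast with 400 mg nor the shape across doses would be estimated.

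A related point bears on null results. The earlier positive result at 400 mg used tetanus toxoid (Introduction), and this trial uses an influenza vaccine. If 50, 100 and 200 mg show nothing, the reading depends on whether 400 mg shows something in this model.

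**Working it through.** **1. The wording side by side.**

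| Place | Doses called lower | Position of 400 mg |
|---|---|---|
| Abstract, Background | 200, 100, 50 mg | already tested |
| Introduction | 200, 100, 50 mg | earlier positive study with tetanus toxoid |
| Research question | 400, 200, 100, 50 mg | one of the lower doses |
| Study hypothesis | no list | not stated |

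The first two rows agree, the third contradicts them, and the fourth inherits whichever is chosen.

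**2. The plan's own sample size, for context.** Inputs from Sample size: d = 0.7, 80% power, 5% significance, 26 per arm. With independent arms (Table 1), n = 2(z_α + z_β)²/d².
- One-sided: 2 × (1.645 + 0.842)²/0.49 = 25.2, rounded up to 26; the exact t calculation gives 25.9. This reproduces the stated 26.
- Two-sided: 2 × (1.960 + 0.842)²/0.49 = 32.0, or 33 after rounding up; the exact t calculation gives 33.0. This does not reproduce 26.

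The article does not state the sidedness, so both are carried below.

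**3. Does the wording change the answer?** Assume that only 400 mg works (0.7 SD over placebo), that 50, 100 and 200 mg do nothing, that 26 per arm are evaluable, that each dose is tested against the shared placebo arm by an unadjusted t-test, and that any significant benefit counts as yes. By simulation (200,000 runs, rechecked with 400,000):

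| Test | Yes, if 400 mg counts | False yes, 50, 100 and 200 mg only |
|---|---|---|
| One-sided 5% | about 80% | about 12% |
| Two-sided 5%, benefit only | about 70% | about 6% |

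If a difference in either direction counts, the two-sided figures are about 74% and 13%.

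**4. How precisely could a lower dose be compared with 400 mg?** The 95% CI half-width for a difference of two means in SD units is 1.96 × √(2/26) = 1.96 × 0.2774 = 0.544 (0.557 with the t quantile on 50 degrees of freedom). With all 30 per arm retained it is 1.96 × √(2/30) = 0.506.

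An illustration with invented estimates: a lower dose at 0.60 SD over placebo and 400 mg at 0.70 SD. The lower dose is significant against placebo (0.60 exceeds 0.557). Its difference from 400 mg is −0.10, with interval −0.10 ± 0.544, that is −0.64 to 0.44. The lower limit allows a loss of 0.64/0.70, about 92% of the 400 mg effect.

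**5. A formal test is out of reach at this size.** The article gives no non-inferiority margin, so I assume a range. At one-sided 0.025 and 80% power the need is 33 per arm for a margin of 0.7 SD, 63 for 0.5 SD and 129 for 0.35 SD. With 26 per arm the power is about 71%, 44% and 24%. An estimate with its interval is the realistic aim.

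**The case against.** The strongest reply is that the dose list in the Research question is the list of active arms carried over from the Objectives, that results will be shown by arm, and that a careful reader would see an effect confined to 400 mg for what it is. The article also states no rule by which any one of four significant doses means yes, so the percentages above depend on a rule that I supplied. Both points stand. They make the problem one of definition, not proof that a wrong conclusion will be drawn. They do not remove the contradiction, because the Study hypothesis has no list of its own.

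A reader might infer more than the article supports:

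- *That every objective compares with placebo only.* Objective (iv) is a correlation, and the Outcomes section speaks of comparisons between groups without limiting them to placebo.
- *That nothing tests whether less than 400 mg is enough to have an effect.* Objectives (i) to (iii) compare 200, 100 and 50 mg with placebo, which is a direct test of whether a dose below 400 mg enhances the response.
- *That 400 mg cannot serve as a check on the influenza model.* Its comparison with placebo is already in objective (i), and nothing says that null results at the other doses would be read without it.
- *That the protocol claims a lower dose equals 400 mg.* The Discussion says only that high concentrations may not be needed to obtain the effect, which can be read as obtaining some effect at less.

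Finally, contrasts and trend tests are often left to an analysis plan, which is not shown. That limits the second half of the point to a mismatch between the stated motivation and the comparisons that the article does name. Whether to use contrasts with 400 mg or a trend is a matter of choice.

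**Conclusion.** The concern holds in limited form. The Research question contradicts the Abstract and Introduction on which doses are lower, and the Study hypothesis leaves the term open, so a benefit at 400 mg alone would satisfy the question as worded. Under the any-dose, unadjusted rule assumed above, the choice of wording moves the chance of a yes from about 12% to about 80% one-sided, or from about 6% to about 70% two-sided counting benefit only, when only 400 mg works.

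The named comparisons answer whether a lower dose beats placebo. They do not answer how it compares with 400 mg, nor the shape of the dose-response that the Introduction and Discussion give as the reason for the trial. There is no numerical error in this point. It warrants a change because the change is cheap and bears on the main conclusion. It says nothing about which dose is preferable.

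**What to change.** - Reconcile the Abstract, Introduction, Research question and Study hypothesis so that the lower-dose hypothesis rests on the 200, 100 and 50 mg arms and 400 mg is named as the previously tested reference. Since the Introduction also describes earlier work at 200 mg and 150 mg, say that 400 mg is the dose for which the article cites a vaccine-challenge result.
- Add one estimate across doses: each of 200, 100 and 50 mg minus 400 mg with a 95% CI, or a dose-response trend. Base any statement on how a lower dose compares with 400 mg on that estimate, not on which doses reach significance against placebo.
- State that null results at the lower doses will be read in light of the already planned 400 mg versus placebo comparison. If 400 mg also shows no benefit, the trial cannot separate ineffective lower doses from an influenza model that did not respond.

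Cost: wording, plus three contrasts or one trend from data already collected. No participants, visits or assays are added. The downside is that intervals against 400 mg of about ±0.54 SD, beside an assumed effect of 0.7 SD, will allow only modest statements.

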### Study hypothesis

The research hypothesis of this study is that daily supplementation of lower doses of TRF will enhance the host’s immune response to an influenza vaccine.

### Outcomes

The primary outcomes of this trial will be comparing the antibody levels to influenza, the blood leucocyte profile, plasma vitamin E and cytokine production between the different groups. Secondary outcomes will be correlating plasma vitamin E levels with immune responses, plasma proteins and gene expression patterns.

## Protocol

### Ethics consideration

The Monash University Human Ethics Committee (MUHREC) have reviewed and approved the study protocol [MUHREC 30401] (27 January 2022). In addition, the study will be conducted in accordance with the principles of the Declaration of Helsinki 2013 and the Malaysian laws on medical research involving human subjects. All changes to changes to the protocol will require approval from MUHREC before they are applied. All data, including personal information about potential and enrolled participants for this study, will be stored in a file kept in a locked cabinet in a locked room in Monash facilities. The digital data will be stored on a secure shared drive behind the Monash firewall. Only the chief investigator will have access to these files. Upon completion of the study, all data will be stored and handled by Monash University Malaysia for at least 15 years after the study has ended. Only researchers listed in the ethics approval will have access to the research data.

This protocol has been registered with the Australian New Zealand Clinical Trials Registry (ANZCTR) [
ACTRN12622000844741] on 15 June 2022.

### Trial design

A single-centre, parallel, double-blinded, placebo-controlled with balanced randomisation into five arms (
Table 1).

**Table 1. T1:** Study groups.

Group	Daily supplementation (Day 0 to Day 56)	Number of volunteers	Influenza vaccine
A	Placebo (0 mg TRF)	30	Day 28
B	50 mg TRF	30	Day 28
C	100 mg TRF	30	Day 28
D	200 mg TRF	30	Day 28
E	400 mg TRF	30	Day 28
	Total volunteers	150	

TRF = Tocotrienol-rich fraction.

### Sample size

The sample size was calculated using
G*Power version 3.1.9.4. With the power set at 80% and a 5% level of significance, the analysis showed that 26 subjects per arm were required to detect a large difference between groups. The effect size (d) was assumed to be 0.7, based on a previous study.
^
19
^ Assuming a 15% dropout rate in two months, 30 subjects per arm (150 subjects) will be enrolled.

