### Statistical analysis

Statistical Package for the Social Sciences (
SPSS) version 18 will be used for the statistical analysis. The mean and standard deviation values will be calculated for each parameter and compared with the baseline and/or placebo. Differences between the baseline and/or placebo will be tested using a paired-t-test when data are normally distributed or Wilcoxon signed-rank when the data are skewed. The significance level will be set as a P value of ≤ 0.05.

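### The 80% power for d = 0.7 with 26 per arm holds for one unadjusted one-sided t-test, which the article does not declare; two-sided, power is about 68–70%

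*Protocol article*

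**What the plan says.** The Sample size section of the protocol article opens its calculation with "With the power set at 80% and a 5% level of significance" and concludes that "the analysis showed that 26 subjects per arm were required to detect a large difference between groups". On the input it says: "The effect size (d) was assumed to be 0.7, based on a previous study". On attrition: "Assuming a 15% dropout rate in two months, 30 subjects per arm (150 subjects) will be enrolled". It gives the software (G*Power) but not the test, the sidedness, or which of the trial's comparisons the power refers to.

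Three other sections bear on this:

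- Trial design describes the study as "placebo-controlled with balanced randomisation into five arms", and the first specific objective is "to compare antibody responses to influenza antigen following daily supplementation with TRF (400, 200, 100 or 50 mg) with placebo". That makes four comparisons with placebo.
- Study hypothesis is worded directionally: "daily supplementation of lower doses of TRF will enhance the host’s immune response to an influenza vaccine".
- Statistical analysis says "The significance level will be set as a P value of ≤ 0.05", again without sidedness.

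The Introduction describes the study from which the effect size was taken as 400 mg TRF daily with a tetanus toxoid vaccine.

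**The concern.** A 5% level given without qualification is ordinarily read as two-sided. On that reading 26 per arm is too few for 80% power at d = 0.7, so the printed inputs and the printed result do not fit together. A reader of the results would take the 80% at face value. If a dose then showed no significant difference from placebo, the chance that a real effect of d = 0.7 had been missed would be taken as 20%, when under two-sided testing it is 30–32%. This matters most for the lower doses, which are what the hypothesis is about.

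**Working it through.** **Inputs.** From Sample size: d = 0.7 (so SD = 1), α = 0.05, power 80%, 26 evaluable per arm, 30 enrolled per arm, 15% dropout. From Trial design: five equal arms. Expected evaluable per arm: 30 × 0.85 = 25.5, hence the range 25–26 below.

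**Method.** Two-sample t-test, equal arms, noncentral t. With n per arm, df = 2n − 2 and noncentrality δ = d√(n/2). One-sided power is P(T > t₀.₉₅), and two-sided power is P(|T| > t₀.₉₇₅), with T noncentral t(df, δ).

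**Step 1: reproduce 26.** At n = 26, δ = 0.7 × √13 = 2.524 and df = 50.

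- One-sided, d = 0.7: critical value 1.676, power 80.1%; the solved n is 25.94, so 26. This matches.
- Two-sided, d = 0.8: the solved n is 25.52, so 26. This also matches, but with a different d.
- Two-sided, d = 0.7: critical value 2.009, power 69.7%; the solved n is 33.02, so 34. This does not match.

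Other tests at d = 0.7 do not give 26 either. A paired t-test needs 15 (one-sided) or 19 (two-sided). A rank test with relative efficiency 0.955 needs 28 or 35. A five-group ANOVA with a largest difference of 0.7 needs about 22, 32, 40 or 50 per arm for the usual patterns of means. To reach 26 per arm (130 in total) it would need f = 0.309, a value the article does not give.

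**Step 2: power at d = 0.7, one dose against placebo, unadjusted.**

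| Evaluable per arm | One-sided 5% | Two-sided 5% |
|---|---|---|
| 25 | 78.7% | 67.9% |
| 25.5 | 79.4% | 68.8% |
| 26 | 80.1% | 69.7% |
| 30 (no dropout) | 85.0% | 76.0% |

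The difference detectable with 80% power, two-sided, is d = 0.81 at n = 25 and 0.79 at n = 26.

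**Step 3: if the four comparisons with placebo are adjusted for.** This uses Dunnett's test with pooled variance over five arms, df = 5(n − 1), and a simulated critical value. Power is per comparison at d = 0.7.

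- Two-sided: critical value about 2.47; power 50.2% at n = 25 and 52.2% at n = 26.
- One-sided: critical value about 2.18; power 61.6% at n = 25 and 63.5% at n = 26.

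Step 3 is conditional, because the article states no adjustment.

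**The case against.** The strongest reply is that nothing has been miscalculated. The figure of 26 is exactly what G*Power's method returns for a one-sided two-sample t-test, the hypothesis predicts enhancement, and no section commits to two-sided testing. Most of this stands. A reader might infer an arithmetic error, and the article does not support that. But a directional hypothesis is not a declaration of a one-sided test, and an unqualified P ≤ 0.05 will be read as two-sided. The gap is an undeclared choice on which the stated power depends.

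Nor can the article show which input is at fault. Since 26 also fits a two-sided test at d = 0.8, and the text calls the difference large, a misreported d is as possible as an unreported one-sided test.

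Three stronger readings should be resisted:

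- **That the trial has only about 50% power.** That figure combines two-sided testing with a Dunnett adjustment, and the article states neither. How multiplicity is handled may be set out in an analysis plan that is not shown.
- **That the stated power can refer only to the 400 mg arm.** The article says d was based on the earlier study. It does not say whether 0.7 is the effect observed there or a discounted value. What can be said is that applying it to the lower doses, and to an influenza vaccine, is an assumption.
- **That the dropout step is a material error.** Dividing gives 26/0.85 = 30.6, so 31, where the plan has 30 (26 × 1.15 = 29.9). The expected shortfall is half a participant per arm, and one-sided power at 25.5 is still 79.4%.

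**Conclusion.** The point holds in a limited form. The stated 80% is correct for one dose against placebo, tested one-sided at 5% without adjustment, with 26 evaluable per arm and d = 0.7. The article does not declare that test. Under the conventional two-sided reading, power for the same d is 68–70% with 25–26 evaluable, about 10 to 12 percentage points below the claim, and 76% if nobody drops out; 80% would need 34 evaluable per arm. Any adjustment for four doses lowers power per comparison further, to about 50–52% two-sided or 62–63% one-sided with Dunnett. These results assume normally distributed outcomes with equal variance, and that d = 0.7 applies to the comparison in question. For the lower doses the article offers no separate support for that value.

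**What to change.** Keep 150 volunteers. In Sample size, name the test and its sidedness and reconcile 26 with d = 0.7. Then take one of two routes:

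- **Two-sided testing.** Restate along these lines: with 25–26 evaluable per arm, a two-sided 5% two-sample t-test has about 68–70% power for d = 0.7 (about 80% for d = 0.8), for one dose versus placebo before multiplicity adjustment.
- **One-sided testing, if intended.** Declare it in both Sample size and Statistical analysis, and say that the 80% is for one unadjusted comparison with 26 evaluable per arm.

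In either case, if the dose comparisons will be adjusted, give the power under that adjustment. Add a sentence saying that d = 0.7 was based on a study of 400 mg with tetanus toxoid and is assumed for the lower doses.

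The cost is a few sentences. No further recruitment follows from it. The downside is a stated power that looks less favourable or, on the one-sided route, an explicit commitment to a one-sided test that readers may question.

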### Criteria for discontinuation

TRF has received the GRAS status from the US FDA.
^
35
^ Hence, severe adverse effects following the consumption of TRF are not expected. However, volunteers can drop out of the study at any time if they experience any side effects or do not want to continue with the study.

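### Thirty per arm falls just short of the stated 26 at the stated 15% dropout (25.5 expected completers): a minor slip in the allowance, worth about one power point

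*Protocol article*

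**What the plan says.** The Sample size section fixes the design inputs as "With the power set at 80% and a 5% level of significance", and adds "The effect size (d) was assumed to be 0.7, based on a previous study". From these it reports that "the analysis showed that 26 subjects per arm were required to detect a large difference between groups". It then allows for losses: "Assuming a 15% dropout rate in two months, 30 subjects per arm (150 subjects) will be enrolled". Table 1 under Trial design repeats 30 for each of the five groups, 150 in all. The article does not show the step that leads from 26 to 30.

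**The concern.** A dropout allowance should make the expected number of completers equal the required number. The enrolled number is therefore the required number divided by the proportion expected to stay. Multiplying by one plus the dropout rate gives too small a figure, because the loss applies to those enrolled and not to those required. The printed 30 looks like the result of multiplying.

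At stake is whether the sample-size statement can be reproduced and whether the power it quotes is the power expected at its own dropout rate. The Objectives compare each TRF dose with placebo, so completers per arm are the relevant count.

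**Working it through.** **Inputs, all from the Sample size section:** required n = 26 per arm; power 80%; significance level 5%, sidedness not stated; d = 0.7; dropout 15%; enrolled 30 per arm, 150 in total.

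**1. Reproducing the 26.** For a two-sample t-test with n per arm, the noncentrality is d × √(n/2) on 2n − 2 degrees of freedom. The smallest n with at least 80% power at d = 0.7 is:
- one-sided 5%: n = 26 (power 80.1%);
- two-sided 5%: n = 34 (power at 26 is 69.7%).

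Other settings tried do not return 26. A paired t-test gives 15 (one-sided) or 19 (two-sided). A rank-test approximation gives 28 to 30 (one-sided) or 35 to 39 (two-sided). The one-sided two-sample test is therefore used below to measure the effect of the dropout slip.

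**2. Reproducing the 30.**
- Multiplying: 26 × 1.15 = 29.9, rounded up to 30. This matches the printed figure.
- Dividing: 26 / (1 − 0.15) = 26 / 0.85 = 30.59, which is 31 whether rounded up or to the nearest whole number.

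**3. Expected completers.**
- 30 × 0.85 = 25.5 per arm, against 26.
- 150 × 0.85 = 127.5 in total, against 5 × 26 = 130.
- With 31 enrolled: 31 × 0.85 = 26.35 per arm.

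**4. Dropout that 30 per arm can absorb.** (30 − 26) / 30 = 4/30 = 13.3%.

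**5. Effect on power (one-sided 5% t-test, d = 0.7).**

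| Completers per arm | Power | Change from 26 |
|---|---|---|
| 26 | 80.1% | – |
| 25.5 | 79.4% | −0.7 points |
| 25 | 78.7% | −1.4 points |

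If each participant in the two compared arms drops out independently with probability 15%, power averaged over the possible numbers of completers is 79.2% with 30 enrolled per arm and 80.4% with 31. The slip is worth about one power point.

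**The case against.** The strongest reply is that this is too small to matter. Half a participant per arm changes power by about a point, and an assumed dropout of 15% is not known closely enough to be told apart from 13.3%. That is right about the consequence, and it is why the point ranks as minor. It does not make the sentence correct: 30.59 does not round to 30, and the conflicting figures stand together in one short section, so a fuller protocol could not reconcile them. It is also fair to say that the cause is inferred. The article gives no formula, and 26 × 1.15 is only a close match.

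Three stronger readings are tempting, and the document supports none of them.

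- *The plan fails to replace participants who leave.* Criteria for discontinuation says only that "volunteers can drop out of the study at any time if they experience any side effects" or no longer wish to continue. It neither provides for replacement nor rules it out, and a condensed article may leave that to the full protocol.
- *The trial will almost certainly miss its target.* With independent 15% dropout, an arm of 30 keeps at least 26 with probability 0.52, and all five arms do so with probability 0.04. But 31 per arm gives only 0.68 and 0.15. These figures mostly reflect chance variation in dropout, and they treat 26 as a cliff although power changes smoothly.
- *One short arm defeats the plan.* An arm of 25 compared with one of 26 has 79.4% power. Nothing in the article makes 26 completers in every arm a condition.

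**Conclusion.** The point holds as a small arithmetical error. At the article's own 15% dropout, 30 per arm gives 25.5 expected completers and not 26; the allowance is one per arm lower than division by the retained share would give. The expected cost is about 0.7 points of power, or 1.4 points if an arm pair ends at 25 each. A reader might infer that the dropout allowance leaves the trial underpowered; it does not.

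The conclusion on counts rests only on printed figures. The conclusion on power assumes a one-sided 5% two-sample t-test at d = 0.7, which the article does not state: Statistical analysis says only "The significance level will be set as a P value of ≤ 0.05". With a two-sided test, power is about 70% at 26 per arm (69.7%) and 68.8% at 25.5. That gap comes from the test behind the 26 and not from the dropout allowance, but it means that any restated power must name the test.

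**What to change.** Enrolment can stay at 150. Replace the last sentence of Sample size with one of two statements:
- 30 per arm allows for a dropout of about 13% (4 of 30) while keeping 26 completers; or
- at 15% dropout, about 25 to 26 completers per arm are expected, giving power of about 79% at d = 0.7 with a one-sided 5% two-sample t-test.

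The second version should be used only if a one-sided test is what was intended. If a two-sided test was intended, the power has to be restated on that basis (about 69% at 25.5 completers per arm). Holding to both 15% and 26 completers would instead take 31 per arm, 155 in total, which is 5 more participants; the size of the effect does not call for it.

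The cost is one sentence of text, once the sidedness behind the 26 has been confirmed, and a slightly less favourable stated figure.
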